### Control group

Patients allocated to the control group will start to breathe in for a count of 3 initiated by the therapist, hold their breath for another count of 3, and then exhale for 10 s from a count of 1. The therapist will also help to increase the patient’s expiratory flow by squeezing the area just above the costal arch on either side to exert pressure on the chest at the end stage of exhalation. The basic articulation training will include multidirectional movements of lips and tongue, the central part of the jaw, and the skin near the temporomandibular joint. Speech training will start from a single vowel (e.g., *a* or *u*) and consonant (e.g., *b*, *p*, *m*) to various combinations of vowel and consonant pronunciations, and gradually to single words and sentences.

### Study group

Patients assigned to the study group will receive Six Character Formula breathing training according to our improved scheme of the Healthcare Qigong Liuzijue instructions edited by the Healthcare Qigong Administration Center of State Physical Culture Administration. The method includes breathing in through the nose and exhaling with annunciation of one of the six different voices and breathing sounds (Xu, He, Hu, Si, Chui, and Xi). At the same time, each sound will be complemented by specific action guidance.

#### Oral guidance key points

Oral guidance key points are the key points of pronouncing and breathing of Liuzijue. For “Xu”, feel the upper and lower teeth (i.e., incisors) force with the two lips parted. For “He”, the strength originates from the root of the tongue, and the mouth is opened naturally. For “Hu”, the power of the voice is in the throat, and the mouth bulges forward like a tube. For “Si”, the power of the voice comes from the teeth when the two lips are slightly open, feeling the corners of the mouth move backwards. For “Chui”, the force is in the central part of the lips, and the middle of the two lips is slightly open. For “Xi”, the power of the voice comes from the upper oral cavity and throat—the two lips are slightly open and the incisors seem to be closed.

Before training, we will inform each patient of the “focus” when he/she breathes and pronounces. We will ask the patient gradually to feel the focus instead of requiring the patient to pronounce forcefully, so as to facilitate the accuracy of pronunciation and breathing.

#### Other key points

A patient with dysarthria after a stroke may have varying degrees of limb hemiplegia and abnormal posture and be unable to sit or stand. Therefore, it is often impossible to complete the action guidance of Liuzijue independently and accurately. Thus, the training position and guide actions cannot be made too rigid. Patients can take an alternative standing, sitting position, etc. A healthy upper limb can drive the affected upper extremity, or the therapist will stand next to the patient to help them complete the action to maintain the normal position of the thorax, spine, and pelvis and to provide a stable mechanical structure. With improvement in the patient’s ability to balance in the standing position, the training position will be gradually transitioned from the sitting position to an independent standing position. With improvement of the upper and trunk functions of the patient, the therapist will gradually reduce the amount of aid. Whether it is active or auxiliary, body movements are based on the principle of mild gentle restfulness. The goal will be to complete the accurate breath guidance protocol.

In addition, the therapist will measure the patient’s decibels before practicing the Six Character Formula and assist them to accomplish target decibel values with increased articulation and respiratory flow.

Basic articulation training will be conducted after training in both the study and control group, consisting of movement training (lips, tongue, and jaws) and pronunciation training from easy to difficult.

### Sample-size calculation

We anticipate that the effective rate of speech breathing-specific curative effect assessed by modified FDA will be 70 and 40% for the study and control groups, respectively. Under such an assumption, 41 participants per group (on a 1:1 ratio) will be needed to show a significant difference at a *P* value < 0.05 with a test power of 80%. Anticipating losses of 18% in follow-ups, we will establish a target sample size of 100 participants (50 participants in each group).

### Statistical analysis

In the study, the main indicator, “speech breathing level according to modified Frenchay Dysarthria Assessment (FDA)”, will be ranked data. The statistical method will be as follows. (1) The main indicator will be compared between baseline and follow-up time with a signed rank test. The score change will be compared between groups using a rank-sum test. Unless indicated otherwise, hypothesis testing will use a two-sided test with *P* = 0.05 as the statistical cutoff point. (2) The influence of rehabilitation intervention time, stroke classification, age, and gender on the efficacy of the intervention method and the relative size of the efficacy will be estimated using a stepwise logistic regression model. (3) The overall efficacy evaluation will be the effective rate. The formula will be: Effective rate = (Excellent + Effective)/Total number of cases × 100%. A chi-squared test will be used to compare any differences in efficacy between the two groups.

The secondary outcomes will be analyzed using a repeated measure covariance analysis with the outcome baseline adjusted for as a covariate. We will test whether there is a statistically significant difference between the groups using a parameter representing treatment allocation. The ‘loudness level’ outcome is ranked data and will be analyzed in a similar way to the primary outcome.

The per-protocol (PP) population will include the randomized patients of the intention to treat (ITT) population but exclude those for whom the inclusion or exclusion criteria were not met and those who did not receive the actual treatments to which the patients were randomly allocated [18]. If the statistical results of the ITT and PP population data are the same, the results will be deemed to be reliable; if they are contrary, we intend to adopt the results of the ITT population. The method of processing missing data will be the last observation carried forward (LOCF). This refers to assigning the last observed value of the end point indicator to the subsequent missing evaluation point; that is, the last observation response will be considered to be the study end point.

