### Primary outcome measurement procedures

Outcome data will be collected at baseline, 1 week, and 2 weeks after the initiation of treatment, and also after the completion of the treatment (third week), by experienced physicians.

The primary measurement will be the speech breathing level of the modified FDA (Table 1).

**Table 1 Tab1:** Specific measurement of speech breathing level assessed by modified FDA

	Baseline	1 week	2 weeks	3 weeks
Speech breathing specific measurement				
Evaluation date				
Signature of therapist				

Speech breathing will be evaluated by letting the patients count to 20 as fast as possible in one breath. They will be assured not to be concerned about the articulation and just the number of breaths necessary to complete the task will be monitored. The normal outcome for this task is the performance in one breath.

The level of speech breathing-specific measurements will be defined as: a) normal and the number of breaths used as the baseline to quantify the seriousness of speech breathing dysfunction; b) the patient needs one additional deep-breath to smooth the speech; c) patient needs four deep breaths due to the disappearance of voice; d) patient needs seven deep breaths due to obvious variability of speech; e) patient spells one word with one breath due to serious impairment of speech. Subjects will be given a score of 1 for grade a, 2 for grade b, 3 for grade c, 4 for grade d, and 5 for grade e. The primary indicator will be the breath assessment of FDA.

The curative effect will be assessed as: 1) CR if the original level degrades ≥ 2 or reduces to the level of grade a; 2) PR if the original level degrades by 1; and 3) NR if the original level does not change or increases.

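### The main indicator has two between-group tests and neither a deciding test nor a deciding visit is named; the sample size was calculated for only one of them

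*Protocol article*

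**What the plan says.** All references are to the protocol article.

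- **Primary outcome measurement procedures:** "The primary measurement will be the speech breathing level of the modified FDA". Grades a to e are scored 1 to 5. The same section defines complete response (CR: improvement of two or more grades, or to grade a), partial response (PR: improvement of one grade) and no response (NR). On timing: "Outcome data will be collected at baseline, 1 week, and 2 weeks after the initiation of treatment", and again when treatment ends in week 3.
- **Statistical analysis, item 1:** "The main indicator will be compared between baseline and follow-up time with a signed rank test", and then "The score change will be compared between groups using a rank-sum test". A general two-sided 0.05 cutoff follows.
- **Statistical analysis, item 3:** "The overall efficacy evaluation will be the effective rate", and "A chi-squared test will be used to compare any differences in efficacy between the two groups".
- **Sample-size calculation:** "We anticipate that the effective rate of speech breathing-specific curative effect assessed by modified FDA will be 70 and 40"%, giving 41 per group for 80% power and 50 per group after 18% loss.

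No order or adjustment is given for the two between-group tests, and no visit is attached to either.

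**The concern.** A trial needs one result that decides whether it succeeded. Here two between-group P values have a claim to that role. The rank-sum test is the between-group test listed for the main indicator. The chi-squared test is the one called the overall efficacy evaluation and the one used for sample size.

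The two use the same data differently. The effective rate asks only whether a patient improved by at least one grade. The rank-sum test also uses the size of the improvement and any worsening. A trial can therefore be positive on one and negative on the other, and nothing in the article says which result stands. At stake are the meaning of the 5% error rate and of the 80% power.

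**Working it through.** **Step 1. Reproduce the stated sample size.** Inputs from the Sample-size calculation section: p1 = 0.70, p2 = 0.40, alpha 0.05 (two-sided, from the Statistical analysis section), power 0.80. The mean proportion is 0.55.

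n = [1.960 × √(2 × 0.55 × 0.45) + 0.8416 × √(0.70 × 0.30 + 0.40 × 0.60)]² / 0.30²
= [1.379 + 0.565]² / 0.09 = 41.97, so 42 per group.

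With unpooled variance the answer is 40, and with the arcsine method 42. The stated 41 is within rounding and method differences. Inflation: 41 / 0.82 = 50, as stated (42 / 0.82 = 51.2, so 52, if the pooled formula is used strictly).

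Power of the chi-squared test = Φ[(0.30√n − 1.379) / 0.671]:
- n = 41: Φ(0.808) = 79.0%
- n = 50: Φ(1.107) = 86.6%

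The calculation is sound for the effective rate.

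**Step 2. Does the 80% carry over to the rank-sum test?** The article gives no distribution of grade changes, so one must be assumed. The effective rates were held at 70% and 40% with 41 per arm, and the mix of one-grade gains, two-grade gains and worsening was varied.
- Rank-sum power ran from about 52% to about 95%. It is low when the extra responders in the study arm gain mainly one grade, and high when they gain mainly two.
- The chi-squared test stayed near 81-82% in the mixes for which it was recorded.
- The two tests gave different verdicts in about 9-30% of simulated trials.

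If every responder gained exactly one grade and nobody worsened, the tests would practically coincide. The range therefore illustrates dependence on the mix. It is not a set of limits, and a more lopsided mix would fall outside it.

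**Step 3. False-positive rate with no true difference.** If the tests were independent, the chance of at least one P < 0.05 would be 1 − 0.95² = 9.75% for two tests and 1 − 0.95⁶ = 26.5% for six. They are strongly correlated, so two null models were simulated.
- Model A: ordinal change scores at three visits, between-visit correlation 0.3-0.9, week-3 effective rate 40-70%, baseline grades b to e, 41 or 50 per arm; 24 scenarios of 4,000 trials.
- Model B: weekly one-grade improvement varying between patients, 41-58% improved by week 3, three baseline mixes, 50 per arm; 2,000 trials per scenario.

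| What may count as success | Model A | Model B |
|---|---|---|
| Either test, week 3 only | 6.1-8.4% | 5.8-7.3% |
| Either test, any of weeks 1, 2, 3 | 14.3-19.9% | 11.4-13.5% |

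In model A each test alone at week 3 ran at 4.1-6.2%, so part of the week-3 excess is simulation error and the coarseness of the data.

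**Step 4. What splitting alpha would cost.** With 0.025 for each of two tests, the effective rate needs 51 per group, and 51 / 0.82 = 62.2, so 63 after loss. Power at 41 per group would be 69.6%. Naming one test avoids this.

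**The case against.** The strongest reply is that the article leans towards the effective rate. It is defined under the primary outcome, used for sample size and described as the overall efficacy evaluation. This stands as a lean. However, the section on objectives names the breathing level itself as the primary indicator and adds the response categories alongside it, and the rank-sum test is listed for that indicator. Nothing says which test prevails.

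A second reply is that the supplementary table of statistical methods, or an analysis plan, may settle the order and the visit. Neither is shown, so that remains possible. The main text still sets out two unranked tests and powers one.

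Several stronger readings are tempting and not supported:

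- **Six tests, so the error more than doubles.** The article says data are collected at three visits, not that the arms are tested at each. Its rule for missing data carries the last observation forward and treats it as the study end point, which suggests a single end point, though no week is named.
- **The tests disagree because a change from b to a is a complete response but only one point.** The effective rate adds the top two categories together, so the CR/PR boundary cannot affect it.
- **The within-group signed-rank tests stand in for a comparison of arms.** Separate between-group tests are given, so this is minor.
- **The secondary model averages the effect over weeks 1-3.** The phrase "using a parameter representing treatment allocation" does not rule out a treatment-by-visit term, and any power loss depends on an assumed build-up of effect.

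**Conclusion.** The point holds in this form: two between-group tests of the main indicator, no deciding test or visit, and a sample size that fits only one of them. The main consequence is for power and interpretation. The stated 80% does not apply to the rank-sum test (about 52-95% under assumed grade mixes), and verdicts differed in about 9-30% of simulated trials with a true 70% against 40% difference.

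The error-rate consequence is modest on the natural reading: about 6-8% if either test may succeed at week 3, or roughly 1.2 to 1.7 times 5%. The figure of about 11-20% applies only if any test at any visit may count, which is a permission the text leaves open but does not state. All simulated figures rest on assumed grade distributions and correlations that are not in the article. The response labels in the effective-rate formula differ from CR and PR; they are taken here to mean the same two categories.

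**What to change.** Name one primary analysis: the between-group comparison at week 3.

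- If it is the chi-squared test of the effective rate, define that rate as CR + PR against NR. The existing sample size then stands (42 per group by formula, 41 stated, 50 planned).
- If it is the rank-sum test of score change, state the assumed distribution of grade changes in each arm and restate the power.

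In either case, label the other between-group test and any week-1 and week-2 comparisons as supportive, and report the signed-rank results descriptively. Make the change before results are known; the article reports recruitment as incomplete at submission.

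The cost is wording only. The analyses not chosen lose confirmatory status.

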**Methods/design:**

The proposed study will be a single-center randomized controlled trial. A total of 100 patients, with a modified Frenchay Dysarthria Assessment (FDA) dysarthria assessment score < 27 and with a FDA speech breathing level ≥ b will be randomly divided into study (*LQG*, *n* = 50) and control (conventional breathing training, n = 50) groups. Basic articulation training will be conducted once a day, five times a week for 3 weeks. Data collection will be conducted at baseline, 1 week, and 2 weeks post-treatment initiation and after completion of the treatment (3 weeks). Comprehensive analyses will be conducted to measure and compare any differences in speech breathing dysfunction levels, comprehensive evaluation of dysarthria, maximum phonation time (MPT), maximal counting ability, signal-noise (S/Z) ratio, and loudness scales between the study and control groups.

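### The rank-sum test on change in speech-breathing grade ignores the baseline grade that limits the change; analysing the 3-week grade with baseline accounted for is a modest, low-cost improvement

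*Protocol article*

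**What the plan says.** The Statistical analysis section calls the speech-breathing level ranked data and fixes its between-group comparison: "The score change will be compared between groups using a rank-sum test". The same section analyses the secondary outcomes "with the outcome baseline adjusted for as a covariate". Loudness is the exception and follows the primary method. The stepwise logistic model lists intervention time, stroke classification, age and gender, but not baseline grade.

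Under Primary outcome measurement procedures the grades are turned into numbers ("Subjects will be given a score of 1 for grade a, 2 for grade b", and so on up to 5 for grade e), and the response rule reads "CR if the original level degrades ≥ 2 or reduces to the level of grade a". A one-grade improvement short of grade a is a partial response. The abstract admits only patients "with a FDA speech breathing level ≥ b will be randomly divided into study" and control groups, so nobody starts at grade a.

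The rank-sum is not the only efficacy test. The overall efficacy evaluation is the effective rate, for which "A chi-squared test will be used to compare any differences in efficacy between the two groups". The Sample-size calculation rests on that rate: 70% vs 40%, 41 evaluable per group, 50 per group after an 18% loss. The Randomization section specifies simple 1:1 randomization, with no stratification.

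**The concern.** Baseline grade is measured in everyone and sets a hard limit on the quantity being ranked. Three consequences follow.

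- **Interpretation.** Equal changes do not mean the same thing at different starting grades, and the ordering by change disagrees with the ordering by response category.
- **Conditional bias.** With unstratified simple randomization the arms may differ by chance in their share of grade-b patients. The arm with more of them has less room to improve, even with no treatment effect.
- **Efficiency.** A covariate that is collected and probably prognostic is left out of this comparison, although it is used for most of the secondary outcomes.

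**Working it through.** **1. The plan's own figure.** Inputs from the Sample-size calculation: 0.70, 0.40, two-sided 0.05, 80% power. The mean proportion is 0.55.

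n = [1.960·√(2·0.55·0.45) + 0.842·√(0.70·0.30 + 0.40·0.60)]² / 0.30² = (1.379 + 0.565)² / 0.09 ≈ 42 per group.

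The unpooled form gives 39.2, so 40. The stated 41 lies between the two; power at 41 is 79.0%. Allowing for loss, 41 / (1 − 0.18) = 50. The figure reproduces, and because it is sized on the effective rate the point below does not alter it.

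**2. Room to improve.** Largest gain = baseline score − 1: b 2 − 1 = 1; c 3 − 1 = 2; d 4 − 1 = 3; e 5 − 1 = 4.

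**3. Change score against response rule.**

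| Move | Score change | Response category |
|---|---|---|
| b to a | 2 − 1 = 1 | complete |
| c to b | 3 − 2 = 1 | partial |
| d to b | 4 − 2 = 2 | complete |

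The rank-sum on change ties the first two, which the protocol separates. It separates the first and third, which the protocol puts together.

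**4. How often the arms differ.** Assume half of patients are at grade b, and take the arms as equal in size (an approximation under simple randomization). With 41 per arm, 20 points is 8.2 patients, so the gap must be at least 9. For two independent Binomial(41, 0.5) counts, P(|difference| ≥ 9) = 6.0%. With 50 per arm the gap must be at least 10, and the probability is 5.7%.

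**5. Rejections given such a gap and no treatment effect.** With grade-b shares of 40% vs 60%, one simulation (500–600 trials per scenario) had the rank-sum on change rejecting in 6.0% (modest recovery) to 11.2% (83% responding in both arms). The baseline-adjusted proportional-odds model rejected in 5.2–7.6%. A second simulation gave 5–10% for the planned test and 4–5% for a rank-sum of the 3-week grade stratified by baseline. With 600 trials the Monte Carlo standard error at 5% is √(0.05·0.95/600) ≈ 0.9 points.

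**6. Power and size over all randomizations.** 41 per group, effective rates calibrated to 70% vs 40%, four assumed baseline mixes, 3000 runs per scenario. All data models are assumptions.

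| Assumed data | Rank-sum on change | Proportional odds, likelihood ratio | Stratified rank-sum |
|---|---|---|---|
| Proportional odds, moderate baseline–outcome link | 84.1–88.5% | 91.3–95.4% | 89.6–93.9% |
| Proportional odds, strong link | 84.5–85.6% | 85.0–86.1% | 82.7–84.0% |
| Same steps in every grade, capped at a | 80.0–80.8% | 83.0–84.2% | 78.7–79.8% |
| Type I error, all scenarios | 4.4–5.8% | 4.8–6.3% | 4.1–5.7% |

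Compared within scenario, the likelihood-ratio version gains 4.4–7.2, 0.5–1.2 and 3.0–3.4 points in the three rows. A score version of the same model holds size at 4.3–5.8%; it gains up to 6.5 points in the first row and is level or up to 1 point below the planned test in the others. The stratified rank-sum ranges from 1.9 points below to 5.5 above. The second simulation, with other assumed mixes, put the stratified test 0 to 14 points above, which shows how far the answer depends on the inputs.

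**The case against.** A rank-sum test on change is conventional, and randomization makes it valid: simulated type I error stayed at 4.4–5.8%. A reader might infer from step 5 that the plan inflates false positives. The documents do not support that. Those rates apply only after an unfavourable draw, and the 11% end needs 83% responding in both arms, above the plan's 40% and 70%. The 6% end is about one Monte Carlo standard error above 5%.

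A reader might also infer that baseline adjustment is better at no cost. It is not. Proportional odds is an added assumption, the likelihood-ratio test is slightly liberal at this size, and in some scenarios nothing is gained.

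A third tempting reading is that the trial's conclusion hangs on a test spoiled by the limit at grade a. The trial is sized on the effective rate. If Excellent and Effective there mean complete and partial response (an assumption, since the labels differ), response is attainable from every eligible grade, including b. Effective rates by arm and the logistic model also give a measure of effect, so the plan is not confined to P values.

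Finally, the Primary and secondary objectives section refers to an additional file for the statistical method. That file is not at hand, so the lack of a baseline term can be stated only of the article.

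All of this stands, and it limits the size of the point. It does not remove the mismatch in step 3 or the case for using a covariate already collected. The chi-squared test does not remove them either: it merges complete with partial response and has no baseline term.

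**Conclusion.** The point holds as a weakness of efficiency, interpretation and conditional bias in the between-group test of the primary grade. It is not an error, and the planned test is not invalid. The bounds on change and the disagreement with the response rule follow directly from the protocol's definitions. The rest depends on assumptions: a gap of 20 points or more in about 6% of trials if half the patients are at grade b, roughly 5–11% null rejections given a 40% vs 60% split, and a power gain of about 0 to 7 points for the ordinal model. The article gives neither the baseline mix nor the strength of the baseline–outcome link, so no single gain can be claimed. A stratified rank test may be level with the planned test or slightly below it.

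**What to change.** Replace the rank-sum on score change with one prespecified analysis of the 3-week grade that accounts for baseline grade. Two forms would serve:

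- a rank-sum test stratified by baseline grade (van Elteren); or
- a proportional-odds model with treatment and baseline grade, reporting the common odds ratio with its 95% confidence interval.

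The form not chosen can be the sensitivity analysis. Treat loudness in the same way, using its own baseline category. Keep the chi-squared test of the effective rate, on which the trial is sized.

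The cost is analysis-plan wording: no new data, visits or patients, and no change to 41 or 50 per group. The model brings a proportional-odds assumption and a likelihood-ratio test with type I error up to about 6% at this size. The stratified rank test avoids both, at the price of slightly lower power in some scenarios. Recruitment was not complete when the article was submitted; the change should be fixed before outcome data are examined by arm.

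### Stepwise logistic regression cannot reliably estimate how the four named factors influence efficacy; one prespecified model should replace it

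*Protocol article*

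**What the plan says.** The Statistical analysis section of the Protocol article has three numbered items for the main indicator. Item (1) compares score change between groups by a rank-sum test. Item (3) compares the effective rate by a chi-squared test. Item (2), between them, has two targets: "The influence of rehabilitation intervention time, stroke classification, age, and gender on the efficacy of the intervention method" and "the relative size of the efficacy". Both "will be estimated using a stepwise logistic regression model".

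The section gives no entry or removal level for the selection, though its general rule is that "hypothesis testing will use a two-sided test with *P* = 0.05 as the statistical cutoff point". It names no interaction terms and does not say whether treatment is held in the model. Baseline speech-breathing grade is not among the four factors, although the secondary outcomes in the same section are adjusted for their baseline value.

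**The concern.** The sentence promises an estimate for each of four factors. Stepwise selection reports only the factors that pass a significance filter. Those that fail get no estimate or interval, and those that pass do so partly because chance pushed their estimates away from zero. The same data choose the terms and then supply the P values and intervals, so these lose their nominal meaning.

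There is also a question of target. Influence on the efficacy of an intervention is effect modification, which is read from treatment-by-factor terms. A model for the size of the efficacy must contain treatment. The text settles neither point.

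At stake is a supportive analysis that could report overstated predictors, say nothing about real ones, and give an exaggerated treatment effect or none.

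**Working it through.** **Inputs from the Sample-size calculation section.** The expected effective rates "will be 70 and 40% for the study and control groups, respectively", and "41 participants per group (on a 1:1 ratio) will be needed to show a significant difference at a *P* value < 0.05" with 80% power. Then: "Anticipating losses of 18% in follow-ups, we will establish a target sample size of 100 participants".

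**The plan's own figure.** With a pooled variance, two-sided 0.05 and no continuity correction:

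n = [1.96·√(2·0.55·0.45) + 0.842·√(0.7·0.3 + 0.4·0.6)]² / 0.30² = 42 per group.

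The unpooled form gives 39.2, so 40. The stated 41 lies between them and has 79.0% power. 41/(1 − 0.18) = 50 per group, or 100 in total. The planning figures are sound and give the two sizes used below: N = 82 evaluable and N = 100 randomized.

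**Simulation assumptions (not in the documents).** Bidirectional stepwise logistic regression with entry P < 0.05 and removal P > 0.10; candidates are treatment and four independent covariates (two standard normal, two binary at 30% and 40%); 600 to 2,000 trials per setting. The true treatment odds ratio is (0.7/0.3)/(0.4/0.6) = 3.5, log 1.25.

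**A real factor effect.** Age with odds ratio 1.5 per SD (log 0.41), other covariates null. The fixed model holds treatment and all four covariates.

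| | N = 82 | N = 100 |
|---|---|---|
| Age retained by stepwise | 38% | 44% |
| Mean log OR when retained | 0.70 | 0.65 |
| Coverage of its 95% CI when retained | 93% | 93% |
| Mean log OR, fixed model | 0.46 | 0.45 |
| Coverage, fixed model | 95% | 95% |

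So 56-62% of trials give no estimate for a factor that matters. The rest report an odds ratio of about e^0.65 = 1.9 to e^0.70 = 2.0 in place of 1.5. A null factor that is retained has an interval covering the truth 0% of the time, because retention means its interval excludes zero. The fixed model has a type I error of 4.8-4.9% for a null factor.

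**If treatment is an ordinary candidate.** With four null covariates, treatment was absent from the final model in 19-21% of trials at N = 82 and 11-14% at N = 100. Arithmetic agrees. With entry at 0.05, treatment is left out about as often as its test is not significant: 1 − 0.790 = 21% at 41 per group and 1 − 0.866 = 13% at 50 per group. When treatment was retained, the mean log odds ratio was 1.48 (OR 4.4) at N = 82 and 1.40 (OR 4.1) at N = 100. Part of that excess is ordinary small-sample bias, since the fixed model's median odds ratio was about 3.7-3.8.

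**Can a fixed model be supported?** Expected non-responders are 50·0.3 + 50·0.6 = 45 at N = 100 and 41·0.3 + 41·0.6 = 36.9 at N = 82. With six single-term covariates that is 45/6 = 7.5 and 36.9/6 = 6.2 per term.

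**Interaction power.** Assume a 50/50 modifier, study-arm rates of 60% and 80%, and 40% in both control strata. The interaction is ln(0.8/0.2) − ln(0.6/0.4) = 0.98. At 25 per cell the standard error is √(3/(25·0.24) + 1/(25·0.16)) = 0.87. Power is Φ(0.98/0.87 − 1.96) ≈ 20%, and 18% at N = 82.

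**The case against.** The strongest reply is that much of this rests on one sentence in a condensed article. The text never says main effects only, and never says that treatment may be removed. Forced terms, interactions and thresholds may be set elsewhere, including the additional file to which the objectives section refers for the method on the primary indicator. That stands: a reader might infer that treatment will be dropped or interactions ignored, but the document only leaves those possibilities open. It does not rescue the selection of the four factors, which is stated.

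Three other tempting readings also fail.

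- **Baseline grade caps the response.** It does not. The article defines "CR if the original level degrades ≥ 2 or reduces to the level of grade a", and PR as a fall of one grade. Only grades b to e are eligible. A one-grade fall therefore makes any eligible patient a responder, if the effective rate counts CR and PR. Grade may still be prognostic, since a grade b patient must reach normal to respond and a grade e patient need not. That is a reason to adjust for it.
- **Stepwise selection causes spurious predictors in 19% of trials.** 1 − 0.95⁴ = 18.5% is the multiplicity of four null tests, and a fixed model would share it. The corresponding 48% needs an entry level of 0.15, which the plan never states.
- **A fixed model is comfortably supported.** It is not. Entering grade as categories makes eight terms, and 45/8 = 5.6 non-responders per term.

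Nor does a fixed model find more factors: it detected the age effect in 39-45% of trials, much like stepwise. Its gain is an estimate with a usable interval in every trial.

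**Conclusion.** The point holds, at moderate to low severity. The stated method does not reliably deliver the stated estimates. Under the assumed thresholds, a moderate real effect goes unreported in more than half of trials and its log odds ratio is overstated by about 60-74% in the rest (0.65/0.41 to 0.70/0.41, from unrounded values). The figures for losing or inflating the treatment effect apply only if treatment is not forced in, which the text leaves open.

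A reader might infer that the trial's main result is compromised. It is not: the rank-sum comparison, the chi-squared comparison and the sample size do not use this model.

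The magnitudes depend on the assumed entry and removal levels, covariate distributions and age effect. It is also assumed that the logistic outcome is the effective-rate response (CR or PR). The direction of the bias does not depend on the exact values chosen.

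**What to change.** Replace stepwise selection with one prespecified logistic model for response at week 3. Retain treatment, baseline speech-breathing grade as a linear score, time since stroke (as the reading of rehabilitation intervention time), stroke type, age as a continuous term, and gender. Report every coefficient with a 95% CI.

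For influence on efficacy, add the treatment-by-factor interactions to this model one at a time, give each with a 95% CI, and label them exploratory.

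The cost is wording only, because all the variables are already named or collected. The limits should be stated with the results: about 6 to 7.5 non-responders per term, and interaction power near 20% in the scenario above, so a wide interval must not be read as absence of effect modification.
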